### Therapist training and trial conditions

The online mindfulness program will be guided by a registered psychologist (AS). These telephone calls will be used to provide support and encouragement and ensure understanding, but will not be used to provide therapy. The project will follow strict manualised protocols under the supervision of a clinical psychologist (LS. Any adverse events will be promptly reported using the Adverse Events reporting guidelines, to the University of Sydney, Human Research Ethics Committee.

### Mindfulness intervention

The online program has been manualized and adapted from [name] Zinn’s MBSR program [11]. It was developed by a registered psychologist (AS) with training in both clinical psychology and mindfulness. It was tailored to the needs and attitudes of PwMS based on a series of 19 face-to-face qualitative interviews that were thematically analysed according to their psychological experiences, difficulties with MS-related symptoms, and responses to questions about the acceptability of the proposed online mindfulness program. The resultant online modules contain fictional case examples of unique characters with different symptom clusters that vary in terms of gender, race, age, disease course and duration that were derived from the interviews. These case examples demonstrate how MBSR techniques can be used to manage a variety of problems that many PwMS face. The five main topics areas of the modules broadly cover: 1) An Introduction to Mindfulness Meditation, 2) Dealing with Stress, 3) Dealing with Difficult Sensations and Emotions, 4) Dealing with Difficult Thoughts, and, 5) Mindful Communication, Compassion and Relapse Prevention. Once created, these modules were then modified and revised based on the suggestions, comments and feedback from a subsample of the original 19 PwMS who viewed the program (*n* = 11). The program was also reviewed by a range of experts (*n* = 8) including three clinical psychologists, two of which have knowledge and extensive training in mindfulness meditation, one clinical neuropsychologist, two neurologists who specialize in MS, one academic emergency physician who has knowledge and experience in the medical treatment of MS and in teaching mindfulness meditation to PwMS, as well as one academic general practitioner who is a mindfulness expert with extensive experience in coordinating the online delivery of mindfulness-based interventions. The three lead authors (AS, LS and SN) then met to discuss each feedback point and determine whether to amend the program in response to that specific feedback.

The mindfulness meditation audio-guides were based on [name] Zinn’s meditation scripts (e.g. Awareness of Breath, Body Scan meditation) and were slightly adapted in the introduction to remind participants about the corresponding module. Suggestions for informal mindfulness practice were also included at the end of each module e.g. “Choose an activity this week that you can do mindfully”, and Mindfulness Logs were created as part of the program to help participants record the type, frequency and duration of meditation practice each week.

### Outcome measures

The primary outcome measure will be depressive symptoms, as measured by the CES-D [37]. The secondary outcomes will include depressive symptoms (PHQ-9), and will be measured online, at baseline, Weeks 1- Week 8, at post-intervention, 3-month and 6-month follow up. All other secondary outcomes, including anxiety (GAD-7 [38]); fatigue (FSS [38]); pain (BPI-SF; [39]), and MS-related Quality of Life (MSIS-29 [40]) and the primary outcome will be measured online at baseline, post-intervention, 3-month and 6-month follow-up.

To investigate factors that may affect treatment success, we will also be measuring several process outcomes. A measure of mindfulness (CAMS-R 10-item [41]) will be administered to all participants at baseline, post- intervention, 3-month and 6-month follow-up in order to investigate whether changes in mindfulness will mediate the relationship between treatment group and treatment outcomes. At post-intervention (Week 9), participants will also be asked to answer online questions about any changes to treatment during the past eight weeks, including whether they started or changed any disease-modifying MS treatments, started seeing a psychologist/ psychiatrist, began or changed the dose of any new mood stabilizing treatments. Participants in the intervention group will complete additional therapy adherence questions (i.e. the type, frequency, and duration of mindfulness meditation) at the end of each week, at 3 and 6-month follow-up. Those in the intervention group will also complete the Credibility/Expectancy questionnaire [42] at the end of Week 1 and questions regarding treatment satisfaction during the last week of the program (Week 8).

The demographic questionnaire administered at the outset of the trial will include questions about patient characteristics (e.g. age, gender, employment status), disease characteristics (e.g. type, duration of MS), current MS-related and mood-stabilizing treatments, and previous experience with psychological therapy and mindfulness meditation. Confirmation of MS diagnosis and type of disease course will be obtained with participants’ permission from their neurologist. The Patient Determined Disease Steps (PDDS) questionnaire [43] will also be administered as part of the demographic data, as a measure of self-reported disability in order to determine whether level of disability moderates treatment outcome.

## Analysis

### Sample size

Our sample size calculation is based on [name] and colleagues’ [9] meta-analysis that found effect sizes of psychosocial interventions ranging from (*d* = 0.2–0.3). According to G*Power, we would need a total sample of 125 to get 80% power with an alpha of .05 including an expected 20% drop-out rate.

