### Statistical analysis

Data will be analysed using intention-to-treat analysis [44]. There are four measurement times, of which three are post-intervention. Linear mixed models will be generated with group as the fixed factor and baseline level of each treatment outcome (e.g. CES-D, GAD-7) as the covariate. Multiple linear regression analyses will also be used to predict change in outcomes over treatment and to investigate the predictive value of potential moderators (i.e. type of MS, depression, fatigue and pain status). Missing data will be minimized using a forced online completion format and participants who are willing will be asked to complete questionnaires even if they drop-out from the online program. Reporting will follow the CONSORT statement [33]. For further information on data management and security, please see Additional file 1.

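### The stated total of 125 for 80% power does not follow from d = 0.2–0.3; an unadjusted comparison has about 17–32% power, and the gain from the planned model depends on a correlation that is not stated

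*Protocol article*

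**What the plan says.** The Sample size section of the protocol article rests on an earlier meta-analysis that "found effect sizes of psychosocial interventions ranging from" d = 0.2 to 0.3. It names no single design value within that range. It then says that, by G*Power, "we would need a total sample of 125 to get 80% power with an alpha of .05 including an expected 20% drop-out rate". It does not give the G*Power test, the sidedness, the allocation ratio or any correlation.

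The Statistical analysis section plans linear mixed models with group as the fixed factor and the baseline value of each outcome as covariate. It adds: "There are four measurement times, of which three are post-intervention". So the number of repeated measurements is stated. Which contrast is primary (one time point or an average over follow-ups) is not. Hypothesis 1, under Aims and hypotheses, names post-treatment, 3 months and 6 months without ranking them.

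**The concern.** The section gives effect size, alpha, power, drop-out and total together, so they can be checked against each other. An effect of d = 0.2–0.3 is small, and a two-arm trial normally needs several hundred participants to detect it with 80% power. A total of 125 is far below that.

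This is the only sensitivity claim in the article. If it stands, a non-significant CES-D result is likely to be read as evidence against an effect of 0.2–0.3, although the trial may have had a modest chance of detecting one.

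**Working it through.** **Inputs.** From the Sample size section: d = 0.2–0.3, power 80%, alpha .05, total 125, drop-out 20% already included. From Statistical analysis: baseline as covariate, three follow-ups. Assumed because not stated: two-sided test, 1:1 allocation, and the correlation ρ between measurements (0.5 and 0.7 shown).

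**Evaluable number.** 125 × (1 − 0.20) = 100, or 50 per arm.

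**Trying to reproduce 125.** The unadjusted number per arm is approximately 2(1.960 + 0.842)²/d², giving 174.4 at d = 0.3 and 392.4 at d = 0.2. The t-distribution raises these to 175.4 and 393.4.

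- d = 0.3: 2 × 176 = 352 evaluable; 352/0.8 = 440 enrolled.
- d = 0.2: 2 × 394 = 788 evaluable; 788/0.8 = 985 enrolled.

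The 100 evaluable are therefore too few by a factor of about 3.5 to 7.9. A one-sided test still needs 348–775 enrolled. Reading the 100 evaluable as a per-arm number gives only 29–56% power. Neither reproduces the stated figure.

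**Unadjusted power at 50 per arm.** The noncentrality is d√(n/2) = 5d, with 98 degrees of freedom.

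- d = 0.2: noncentrality 1.00, power 16.8%.
- d = 0.25: noncentrality 1.25, power 23.6%.
- d = 0.3: noncentrality 1.50, power 31.8%.
- 80% power is reached at d = 0.566 (normal approximation: 2.802 × √(2/50) = 0.560).
- One-sided, the range is 26–44%.

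**Power under the planned type of model.** Baseline adjustment multiplies the variance by v, and the noncentrality becomes 5d/√v (97 degrees of freedom).

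- One time point: v = 1 − ρ².
- Mean of three follow-ups: v = (1 + 2ρ)/3 − ρ². This assumes compound symmetry, the same effect at each follow-up and no missing data among the 100.

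| Contrast | ρ | v | Power, d = 0.2 | Power, d = 0.3 | d for 80% |
|---|---|---|---|---|---|
| One time point | 0.5 | 0.750 | 21% | 40% | 0.490 |
| One time point | 0.7 | 0.510 | 28% | 55% | 0.404 |
| Mean of three | 0.5 | 0.417 | 34% | 63% | 0.365 |
| Mean of three | 0.7 | 0.310 | 43% | 76% | 0.315 |

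The normal approximation gives 0.362 and 0.312 for the last two entries in the final column.

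**Correlation needed for the stated 80%.** At 50 per arm, 80% power needs a noncentrality of about 5 × 0.566 = 2.83, so v must not exceed (5d/2.83)². That is 0.281 at d = 0.3 and 0.125 at d = 0.2. Solving for ρ:

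- Mean of three: about 0.74 at d = 0.3; about 0.90 at d = 0.2.
- One time point: about 0.85 at d = 0.3; about 0.93 at d = 0.2.

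**The case against.** The strongest reply is that the unadjusted t-test is not the planned analysis. The article plans baseline adjustment and three follow-ups, and both add power. This stands, and it limits the point. A reader might infer that the trial has only 17–32% power, or can detect nothing smaller than d = 0.57. The documents do not support that, because those figures belong to an unadjusted single-time-point test. At d = 0.3 and ρ = 0.7, power is 55% at one time point and 76% for the mean of three. With a high enough correlation the stated 80% could be met at d = 0.3. The reply does not rescue the sentence as written: it invokes no correlation or averaged contrast, and the lower end of its own range needs ρ of about 0.90 even with averaging.

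A reader might also infer a particular slip in G*Power, such as a d value entered where another effect-size scale was expected. Several settings land near 125, but the article does not say which was used, so the cause cannot be established.

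The Background cites d = 0.8 for depression in a face-to-face mindfulness trial, which 100 evaluable participants would detect easily. The calculation nevertheless rests on 0.2–0.3, and that is the claim being checked.

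Finally, the missing detail might be thought a matter for a fuller document. That would excuse an omission, but the section states an effect range, a power and a total that do not fit together.

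**Conclusion.** Wrong as written. No standard two-sample calculation takes d = 0.2–0.3, 80% power and alpha .05 to 125 enrolled. With two-sided testing and 1:1 allocation assumed, power in an unadjusted single-time-point comparison is about half to a fifth of the stated 80%. The planned model narrows the gap by an amount the article leaves undetermined. At correlations of 0.5 to 0.7 power stays below 80% across the whole stated range, whether one time point or the mean of three is used. The averaged figures are favourable to the plan, since they assume equal effects and complete follow-up among the 100 evaluable.

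It does not follow that the trial must enrol 440 to 985 participants, or that it cannot detect a larger effect. The finding concerns the stated sensitivity, which the section's own inputs do not support.

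**What to change.** Keep the total of 125. In the Sample size section:

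- Name the test, sidedness, allocation ratio, design value of d, assumed correlation and primary CES-D contrast.
- Replace the 80% claim with the recomputed power, or the detectable d, for the planned baseline-adjusted model over a range of correlations. Give the unadjusted single-time-point figure alongside. If the assumptions used here are adopted, the table above supplies the values.
- Commit to reporting the CES-D confidence interval against d = 0.2–0.3, and say that a non-significant result does not by itself exclude an effect of that size.

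The cost is wording only, with no extra participants or assessments. The stated sensitivity becomes less favourable.

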### Statistical analysis

Data will be analysed using intention-to-treat analysis [44]. There are four measurement times, of which three are post-intervention. Linear mixed models will be generated with group as the fixed factor and baseline level of each treatment outcome (e.g. CES-D, GAD-7) as the covariate. Multiple linear regression analyses will also be used to predict change in outcomes over treatment and to investigate the predictive value of potential moderators (i.e. type of MS, depression, fatigue and pain status). Missing data will be minimized using a forced online completion format and participants who are willing will be asked to complete questionnaires even if they drop-out from the online program. Reporting will follow the CONSORT statement [33]. For further information on data management and security, please see Additional file 1.

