### Aims and hypotheses

The aim of the current study is to evaluate the efficacy of an online mindfulness-based program for symptoms of depression, anxiety, fatigue, pain and health-related quality of life in PwMS. Whilst mindfulness is a centuries-old tradition stemming from Buddhist philosophy, the current scientific interest in mindfulness as a treatment for mental health problems started as a method to prevent depressive episodes in people with a history of depression who were currently asymptomatic. Evidence supports the efficacy of mindfulness for the prevention of recurrence of depression [29]. Since a large proportion of PwMS develop major depression (50% lifetime prevalence [30]), the ability of mindfulness to prevent future relapse of depression amongst those with a history of depression may be particularly valuable in the management of PwMS. Furthermore, whilst Grossman et al. (2010) did not examine depressive disorders or relapses of depression, there is evidence in the rheumatoid arthritis (RA) literature that while CBT was more effective overall than MBSR, for those patients who had a history of recurrent depression (two or more episodes), mindfulness outperformed CBT [31]. Given that the prevalence of clinically significant depression in people with rheumatoid arthritis is estimated to be approximately 16% [32] and the rate is considerably larger for PwMS, the potential benefits of mindfulness may be greater in MS. Therefore, a secondary aim of this study is to determine whether PwMS with a history of recurrent depression will benefit significantly more from the online mindfulness program than those without. We define recurrent depression as having two or more episodes of depression, consistent with work in RA [31]. If there are insufficient numbers to test the recurrent depression hypothesis, we will examine whether having any history of lifetime depression (current or history) is a moderator of treatment effect. To elucidate the likely mechanisms of treatment gains, we will examine whether changes in the state mindfulness will mediate the effect between treatment group and treatment outcomes, and whether adherence to mindfulness practice predicts outcome in the treatment group.

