We hypothesize that **(1)** PwMS who participate in the online mindfulness intervention will demonstrate significant improvements in depressive symptoms (primary outcome), anxiety, fatigue, pain and HRQOL outcomes at post-treatment, 3-month, and 6-month follow-up, compared with waitlist controls; **(2)** PwMS with a history of recurrent depression will benefit significantly more from the online mindfulness program than those without; **(3)** Changes in mindfulness will mediate the effect between treatment group and treatment outcomes; **(4)** PwMS that report greater meditation adherence will have greater improvements in outcomes than those without.

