### Randomisation

Randomisation will be stratified by history of major depression (assessed via the PRIME-MD). This will be performed by a researcher who will have no contact with participants throughout the duration of the trial, using computer-generated random numbers.

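### The moderator analysis is a regression predicting change with no group-by-moderator term named, so as worded it estimates prognosis and does not test Hypothesis 2

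*Protocol article*

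**What the plan says.** All references are to the protocol article.

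- **Aims and hypotheses.** Hypothesis 2 is that "PwMS with a history of recurrent depression will benefit significantly more from the online mindfulness program than those without". Recurrent means two or more episodes. If numbers are too small, the fallback is that "we will examine whether having any history of lifetime depression (current or history) is a moderator of treatment effect".
- **Outcome measures.** The disability questionnaire (PDDS) is collected "in order to determine whether level of disability moderates treatment outcome".
- **Randomisation.** Allocation is stratified by history of major depression.
- **Statistical analysis, main model.** "Linear mixed models will be generated with group as the fixed factor and baseline level of each treatment outcome" is the covariate. No moderator appears in this model.
- **Statistical analysis, moderators.** "Multiple linear regression analyses will also be used to predict change in outcomes over treatment and to investigate the predictive value of potential moderators". The variables follow after an i.e.: "type of MS, depression, fatigue and pain status". Neither the other covariates of this regression nor any product term is given.

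**The concern.** A moderator is a variable across which the difference between programme and waitlist varies. That is a contrast of contrasts, estimated by a group-by-moderator term. A coefficient for a variable that predicts change says only that people with that characteristic change more or less, whichever arm they are in. The two questions have different answers, and the aims ask the first while the stated method describes the second.

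There is a further hazard when the dependent variable is change. People who start high on a scale tend to fall, and people who start low tend to rise, with or without treatment. If depression, fatigue or pain status means the baseline level of an outcome whose change is being predicted, an association is built in. The trial could then report that more depressed, fatigued or pained people benefit more when the benefit is the same for everyone, or absent. Such a statement could influence who is offered the programme.

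The list of moderators also does not match the aims it is meant to serve.

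**Working it through.** **1. Compare the aims with the listed moderators.**

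| Variable | Where moderation is intended | In the Statistical analysis list? |
|---|---|---|
| Recurrent depression (two or more episodes) | Aims; Hypothesis 2 | Not named; only depression, which could mean current severity or history |
| Any lifetime depression | Aims (fallback) | Not named as such |
| Disability (PDDS) | Outcome measures | No |
| Type of MS, fatigue status, pain status | Statistical analysis only | Yes |

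The list is introduced as complete (i.e., not e.g.), so the mismatch lies within the article and does not depend on any fuller plan.

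**2. Inputs for the size of the artefact.** The article gives no figure for moderation. Its Sample size section says "we would need a total sample of 125 to get 80% power with an alpha of .05 including an expected 20% drop-out rate", so completers are 125 × 0.80 = 100. How 125 was derived does not bear on this point. Assumptions not in the documents: 1:1 allocation (50 treated completers), equal variance before and after, and pre-post correlation r between 0.5 and 0.8.

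**3. Regression to the mean, continuous baseline score.** With no moderation and baseline not adjusted for,

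corr(change, baseline) = −√((1 − r)/2).

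At r = 0.6 this is −√0.20 = −0.45. The chance of p < .05, from the noncentral t distribution, is:

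| r | correlation | 100 completers | 50 treated only |
|---|---|---|---|
| 0.5 | −0.50 | 100% | 98% |
| 0.6 | −0.45 | 99.9% | 93% |
| 0.7 | −0.39 | 99% | 83% |
| 0.8 | −0.32 | 91% | 64% |

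**4. Status as a median cut of the same baseline score.** Simulation used 100 completers and the same treatment effect (d = 0.3) for everyone, so there is no true moderation. The cut is significant in 88–99% of trials (r = 0.7 to 0.5), or 62–85% in the treated arm alone. At r = 0.8 the cut's correlation with change is about 0.80 × 0.32 = 0.25, and the rate falls to about 70%. Adding group as a main effect does not help (89–99%, r = 0.7 to 0.5). Adding the baseline score returns the rate to about 5%.

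**5. Variables that are not the baseline of the same outcome.**
- A status variable correlating 0.5 with the baseline outcome: 37–71% (r = 0.8 to 0.5).
- A depression history with a baseline gap of 0.5–1.0 SD that partly regresses: 16–68% (r = 0.7 to 0.5).
- The same history with a stable gap: about 5%. In that case, however, the history's main effect in a baseline-adjusted model is significant in 18–71% of trials. That is a correct finding about prognosis, and it would be misread as moderation.

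**6. The group-by-moderator term.** In a baseline-adjusted model it stayed at about 4–6% in all these scenarios.

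**7. Power of that term.** With N completers and moderator prevalence p, in SD units,

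SE² = (1 − r²) × (4/N) × (1/p + 1/(1 − p)).

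- p = 0.25, r = 0: SE² = 0.04 × 5.33 = 0.213, SE = 0.46. Detectable at 80% power: 2.80 × 0.46 = 1.29 SD.
- p = 0.50, r = 0.7: SE² = 0.51 × 0.04 × 4 = 0.082, SE = 0.29. Detectable: 2.80 × 0.286 = 0.80 SD.

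Across this range two-sided power is 10–18% for an interaction of 0.3 SD and 25–56% for 0.6 SD.

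**The case against.** The strongest reply is that the article is a condensed account. One sentence covers these regressions, and it neither includes nor excludes an interaction. The aims speak of moderating the treatment effect, so the intention is right and a fuller plan may hold the model terms. The sentence just before makes the baseline score a covariate in the mixed models. If that carries over, the regression-to-the-mean artefact disappears.

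Much of this stands, and it rules out three stronger readings that a reader might infer:

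- **That an interaction is excluded.** The text does not say so. It only fails to name one.
- **That Hypothesis 2 is left untested.** The aims commit to examining it and give a fallback, randomisation is stratified by depression history, and depression is on the list. What can be said is that the stated analysis does not show how the test is done.
- **That the listed moderators will nearly always come out significant.** That holds only if baseline is omitted and status is the baseline score of the same outcome. It does not apply in the same way to type of MS or to a stable history.

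What the reply does not answer is that the article does more than stay silent. It names a method, a dependent variable (change) and a target (predictive value), and that combination describes prognosis. Adding baseline removes the artefact but leaves a main effect, which still does not address differential benefit. The mismatch in the moderator lists remains in any case.

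**Conclusion.** The point holds in this limited form. As worded, the moderator analysis estimates prognosis, and neither stated model contains the term that would test Hypothesis 2 or the disability question. The list of moderators conflicts with the aims and with the Outcome measures section.

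The size of the possible error depends on choices that the article does not state. It is large in the worst case (a baseline score of the same outcome, unadjusted), intermediate for related variables, and absent for a stable history regressed on unadjusted change. The correlations, prevalences, baseline gaps and 1:1 allocation are assumptions.

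Severity is moderate. The aims affected are secondary or exploratory, and the baseline-adjusted group comparison on the primary outcome is untouched.

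**What to change.** Replace the change-score regression, for moderators, with the baseline-adjusted mixed model of the follow-up scores, adding the moderator's main effect and its product with group. Where the moderator is the baseline score of the same outcome, the existing covariate serves as the main effect and only the product is added.

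- Name recurrent depression (two or more episodes) as the prespecified moderator for Hypothesis 2, with the stated fallback to any lifetime depression.
- Add PDDS to the list, beside type of MS and baseline depression, fatigue and pain, and say that these are baseline levels if that is what status means.
- Report each interaction estimate with its 95% confidence interval. Interpret all of them, including the one for Hypothesis 2, as exploratory. With about 100 completers a confirmatory label is not supportable, and a non-significant interaction would not show that benefit is equal.

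The cost is a revised paragraph and slightly more analysis work, with no new data. Fewer moderators are likely to reach significance.
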